#### 6.9.4. Analysis of Secondary Endpoints

##### 6.9.4.1 Safety and Risk Behavior Data.

Reactogenicity, adverse events and serious adverse events will be tabulated both overall and by study arm. Frequencies of specific safety events will be compared across study arms using a chi-square test to evaluate the null hypothesis that safety event rates are the same in both study arms.

Risk assessment data from the ‘Baseline’ and ‘Interval’ Risk Assessment CRFs will be tabulated both overall and by study arm. These questionnaires collect reported behavior data. The data will be analyzed for changes in behavior. Frequencies of specific risk behavior events at baseline and during follow-up will be compared across study arms using chi-square tests to evaluate the null hypothesis that the event rates remain the same. Specific risk behavior events will be compared (see Behavioral Risk Assessment). Repeated measures analyses of binary data will be performed to evaluate changes in the prevalence of these behaviors over time, overall and between the treatment groups. In addition, changes over time in proportions exhibiting specific behaviors will be assessed using McNemar’s test. Participation impact events (from PIE CRFs) will also be tabulated overall and by study arm. Frequencies of events throughout the course of the study will be compared across study arms using chi-square tests to evaluate the null hypothesis that the event rates are similar in both study arms.

Previous studies using ALVAC-HIV (vCP1521) and AIDSVAX® B/E have shown that these vaccines alone and in combination (11,52) have good safety profiles. Previous and ongoing HIV vaccine studies conducted in Thailand have shown little evidence of increase in risk-taking behavior (27; TAVEG unpublished data). However, given the theoretical concern that antibodies generated by the prime-boost combination may prove to be enhancing, HIV infection rates in both groups will be monitored (as per previous analysis). In addition, the rate of disease progression as measured by viral load and CD4 count among infected vaccine recipients will be compared to the corresponding rates in placebo recipients.

The DCAC will provide data on safety and participation impact events quarterly to an independent statistician who is not a member of the DSMB. This statistician will have the ability to consult/confer with the DSMB if, in his/her opinion, there is significant asymmetry in the occurrence of HIV infection, AEs, SAEs, viral load and CD4 count at set point between the vaccine and placebo groups, or increased risk-taking behavior and adverse participation impact events. In the latter two cases, changes in counseling may need to be made to reduce risk-taking

behavior or intervention from study staff may be needed to assist participants experiencing particularly unfavorable events due to their participation.

Interim safety monitoring will include looking for significantly higher rates of infection in the vaccine arm. Prior to the start of the trial, guidelines will be determined by the DSMB and the independent statistician that help to establish the need and frequency for DSMB safety reviews. The Z statistic for the hazard ratio at interim safety analyses will be compared to a continuous stopping boundary (58). A Type I error rate of 0.10 will be specified. Continuous stopping boundaries maintain Type I error and provide a flexible method for monitoring an ongoing trial by allowing for more frequent safety monitoring when the boundaries are almost crossed. If the boundary is crossed, a DSMB meeting will be convened and it is anticipated that the trial will be stopped. If the Z statistic approaches but does not exceed the continuous stopping boundary, this could raise concerns about the possibility of enhancement of the investigational vaccine, and the statistician will alert the DSMB chairperson. Such rules in addition to all relevant data will serve as guidelines for the DSMB in its decision-making process.

#### **6.9.4.2 CD4 T cell counts.**

CD4+ T cell counts will be compared between infected vaccine recipients and infected placebo recipients. Statistical comparisons will be carried out using the nonparametric Mann-Whitney test. CD4+ T cell counts will be measured at the time of diagnosis of HIV infection and during subsequent follow-up. Statistical power of a test for differences in CD4+ T-cell counts between infected vaccine recipients and infected placebo recipients was calculated. The calculations assume that vaccine efficacy is 50% post-immunization (25% prior to full immunization) and that the comparison is made between CD4+ T cell counts measured 6 months post-diagnosis of HIV infection. The standard deviation was assumed to be approximately 235, and the mean among infected placebo recipients was assumed to be 505. The mean and standard deviation were obtained using the values reported for the mean and range of CD4+ T cell counts in subtype E infections (59). For the calculations below, the standard deviation was estimated to be the reported range divided by 4. Detectable differences were calculated for a 2-sided non-parametric Mann-Whitney test at a significance level of 0.05 for power of 80% and 90%. Detectable differences were calculated using PASS 2000 with nonparametric adjustment to a t-test. Under the anticipated study design, there are expected to be approximately 43 infected vaccinees and 78 infected placebo recipients, including 10 vaccinees and 13 placebo recipients who become infected before complete immunization. As Table 6 shows, if the CD4+ T-cell counts in the two groups differ by 26% or more, then this difference should be detectable by an intent-to-treat analysis with the current study design with at least 80% power if the expected number of infections occur.

**Table 6.** Detectable differences in CD4+ T cell counts for 80% and 90% power – intent-to-treat and per-protocol analyses.

| Type of Analysis | VE  | Infected Vaccine Recipients (#) | Infected Placebo Recipients (#) | Detectable Difference (% of Placebo Mean) |             |
|------------------|-----|---------------------------------|---------------------------------|-------------------------------------------|-------------|
|                  |     |                                 |                                 | 80% Power                                 | 90% Power   |
| ITT              | .30 | 57                              | 78                              | 118.7 (24%)                               | 137.4 (27%) |
| ITT              | .50 | 43                              | 78                              | 129.3 (26%)                               | 149.6 (30%) |
| ITT              | .60 | 35                              | 78                              | 139.1 (28%)                               | 160.9 (32%) |
| Per-Protocol     | .30 | 46                              | 65                              | 131.9 (26%)                               | 152.6 (30%) |
| Per-Protocol     | .50 | 33                              | 65                              | 146.4 (29%)                               | 169.4 (34%) |
| Per-Protocol     | .60 | 26                              | 65                              | 160.1 (32%)                               | 185.3 (37%) |

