d) Those volunteers who become HIV infected will continue to participate in the trial. Through the remainder of the trial after HIV infection is diagnosed, follow-up visits will be scheduled every 6 months (consistent with original study schedule) for counseling and follow-up safety assessments, CD4 count, viral load, virus isolation (if not previously successful), drug resistance testing (if on anti-retroviral drugs), other genetic characterization of infecting viruses (sieve analysis) and archives of plasma and PBMC (see Section 6.7.3). Concomitant medications used in association with an adverse event will be elicited and recorded on source documents and CRFs. Laboratory results of CD4 count and viral load/drug resistance testing will be provided confidentially to the treating physician. The timing of these follow-up visits is intended to help maintain confidentiality of the HIV status of the volunteer. Throughout the duration of the trial, blinding will be maintained for these infected volunteers, as for uninfected volunteers in the trial.

e) It is recognized that few clinical endpoints (AIDS-defining illnesses, CD4 count < 200, death) will occur among infected volunteers during the duration of this protocol (53). In order to gather this important, but supplementary, information, it is intended that a separate protocol will be developed and submitted through the full review and approval process.

f)

f) As the RV152 protocol, which follows breakthrough infections in RV144, is allowed access to RV144 information in order to provide additional data for analysis, viral load and CD4 data collected in RV152 can be utilized in RV144. In addition, clinical samples will be shared between RV144 and RV152 to address study objectives in the two studies.

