### **Secondary Endpoints**

#### **Changes in CD4 Cell Count**

CD4 counts add prognostic value to viral load in terms of rate of disease progression (57). Two CD4 cell counts will be obtained (at the verification blood draw and the notification blood draw) and through the remainder of the follow-up period. Results will be compared in vaccine and placebo recipients who become HIV-infected during the trial. The trial is powered to detect a 26% difference in CD4 count between vaccine and placebo groups (see Section

---

 Please see Analytic Addendum, **Section 18**, for primary analyses.

6.9.42).

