**Total blood volume: 78 mL**

 Will include standard EIA and WB; also nucleic acid tests if serology suggestive of infection.

 Will be performed in HIV-infected volunteers as part of verification blood draw, at time of giving diagnosis of HIV infection and then every six months until the completion of the trial.

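### The CD4 power statement counts infections first found at the last visit, which have no 6-month CD4 count in this trial; on RV144 data alone, power for a 26% difference is about 76%, not at least 80%

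*Protocol*

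**What the plan says.** Section 6.9.4.2 assumes for its power calculation that "the comparison is made between CD4+ T cell counts measured 6 months post-diagnosis of HIV infection". The case numbers are those expected over the whole trial: "there are expected to be approximately 43 infected vaccinees and 78 infected placebo recipients". The other inputs are given as follows: "The standard deviation was assumed to be approximately 235, and the mean among infected placebo recipients was assumed to be 505". On method: "Detectable differences were calculated using PASS 2000 with nonparametric adjustment to a t-test". For the intent-to-treat row at 50% efficacy, Table 6 gives 129.3 cells (26% of the placebo mean) at 80% power. The text claims at least 80% power for 26% under the current design, provided the expected infections occur. The CD4 paragraph of Section 6.7.1 repeats the figure without qualification: "The trial is powered to detect a 26% difference in CD4 count between vaccine and placebo groups".

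Section 6.6 sets the last HIV test at Visit 19, week 182. Visit 20, about 2 to 3 weeks later, completes the termination form. Note b to the testing algorithm in Section 6.7.3 makes clear that infections found at Visit 19 still count. For infected volunteers, footnote 2 to the Section 6.8 flow chart schedules CD4 counts at the verification draw, "at time of giving diagnosis of HIV infection and then every six months until the completion of the trial". The algorithm in Section 6.7.3 starts the 6-monthly clock at the visit where infection was first suspected.

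Section 6.5.1, item f), adds that "viral load and CD4 data collected in RV152 can be utilized in RV144".

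**The concern.** A volunteer first found positive at Visit 17 has the 6-month count at Visit 19. A volunteer first found positive at Visit 19 has the verification and notification counts, and then the trial is over. The power calculation nevertheless treats every expected infection as supplying a 6-month count. The stated power therefore rests on more observations than the visit schedule can deliver, even if exactly 43 and 78 infections occur.

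At stake is the accuracy of a figure that the protocol states in Section 6.7.1, Section 6.9.4.2 and Table 6 for a named secondary endpoint. No decision rule and no sample size depends on it.

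**Working it through.** **Inputs.** 8,000 per arm; placebo incidence 0.34% per year; 5% loss per 6 months; efficacy 25% during immunization and 50% after (Sections 6.9.2 and 6.9.3.1, Appendix 17.6). SD 235, placebo mean 505, two-sided 0.05, Mann-Whitney test (Section 6.9.4.2). 26% of 505 is 131.3 cells.

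**Step 1: reproduce Table 6.** I used a two-sample noncentral t with each group size multiplied by the Mann-Whitney efficiency 3/π. The standard error is then SE = 235 × √(π/3) × √(1/n₁ + 1/n₂).
- For 43 and 78, SE = 45.7 cells. The detectable difference at 80% power is 129.1, against 129.3 stated.
- Power is 80.1% at 129.3 cells and 81.3% at 131.3 cells.
- The other Table 6 rows at 80% power agree within about 1.3%.

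**Step 2: do the 43 and 78 include the last visit?** Infections per half-year are the number at risk at the start × 0.975 × 0.5 × hazard. The placebo hazard is −ln(1 − 0.0034) = 0.003406, and the number at risk falls by 5% and by the infections in each interval.
- Placebo: 13.28, 12.60, 11.95, 11.33, 10.74, 10.19, 9.66; total 79.7.
- Vaccine: 9.96, 6.30, 5.98, 5.68, 5.39, 5.11, 4.85; total 43.3.

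The totals match the stated 78 and 43 only with the last interval included. Without it they would be about 70 and 38.

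**Step 3: remove Visit 19 cases.** The last-interval shares are 9.66/79.7 = 12.1% (placebo) and 4.85/43.3 = 11.2% (vaccine). Then 78 × 0.879 = 68.5 and 43 × 0.888 = 38.2. Spreading dropout uniformly (30.2% cumulative) gives the same result: 68.6 and 38.2.

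**Step 4: power with the usable cases.** For 38.2 and 68.5, SE = 48.6 cells and the noncentrality at 131.3 cells is 131.3/48.6 = 2.70.

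| 6-month counts available | Vaccine / placebo | Power at 26% (131.3) | Detectable at 80% |
|---|---|---|---|
| All infections (as in Table 6) | 43 / 78 | 81% | 129 (26%) |
| Half of Visit 19 cases, through RV152 | 40.6 / 73.3 | 79% | 133 (26%) |
| No Visit 19 cases (RV144 alone) | 38.2 / 68.5 | 76% | 137 (27%) |
| RV144 alone, and 5% of the rest lost (assumption) | 36.3 / 65.1 | 74% | 141 (28%) |

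At the table's own 129.3 cells, RV144 data alone give 75.1%.

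**Step 5: per-protocol row at 50% efficacy.** Leaving out the immunization phase, the last-interval shares are 9.66/66.5 = 14.5% (placebo) and 4.85/33.3 = 14.6% (vaccine). The stated 33 and 65 become about 28 and 56, and the detectable difference moves from the stated 29% to about 31%.

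**The case against.** The strongest reply is that the protocol already has a route to the missing counts. RV152 follows breakthrough infections, and Section 6.5.1 f) lets its CD4 data be used. This largely stands as a limit on the size of the shortfall. RV152's uptake and visit schedule are not in the document, so 76% is the case of no recovery. It does not remove the point, because item f) is a permission and the power statement neither mentions nor assumes RV152.

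A reader might infer more than the document supports:
- **That the 26% needs an RV152 count from every Visit 19 case.** It does not. Recovery of half of them already gives about 79% power and a detectable difference that rounds to 26%.
- **That the schedule alone brings the figure to 28%.** It does not. That takes a further 5% loss among diagnosed volunteers. Appendix 17.6 calls 5% an upper bound on loss for the intent-to-treat analysis, because it also covers missed vaccination windows. Applying it to diagnosed volunteers is an assumption.
- **That the CD4 analysis itself is restricted to 6 months, or should move to the diagnosis-time counts.** The 6-month point is an assumption of the power calculation. Sections 6.7.1 and 6.9.4.2 already plan counts from diagnosis onward, and which count should lead is a matter of judgement.

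Input uncertainty is also at least as large as the correction. The SD is an approximation, a reported range divided by 4. With an SD of 225, the detectable difference is 26.0% even with every Visit 19 case excluded. At the 0.68 per 100 person-years observed in 20 to 30 year olds (Section 6.9.2), twice the planning rate, case numbers would double and power at 26% would be about 96% even after the added 5% loss. These uncertainties keep the point minor. They do not make the stated figure follow from its stated inputs.

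**Conclusion.** The point holds in a limited form. On the protocol's own inputs and RV144 data alone, the 6-month CD4 comparison has about 38 and 68 cases, about 76% power for a 26% difference, and a detectable difference of about 27% (137 cells) at 80% power. With RV152 data the figure lies between this and the stated one, depending on a recovery share that the document does not give. Losses among diagnosed volunteers would lower it; at an assumed 5% it is about 74% power and 28%.

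The result rests on the planning incidence, dropout and efficacy, an SD of 235, and the 3/π adjustment that reproduces Table 6. It is a shortfall of about 5 percentage points for a secondary endpoint. It does not invalidate the CD4 analysis: a null result would be read from its confidence interval and not from Table 6.

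**What to change.** - Recompute Table 6, intent-to-treat and per-protocol rows, using only infections that can have a 6-month visit within RV144, meaning those found by Visit 17.
- Restate Sections 6.7.1 and 6.9.4.2 as about 27% at 80% power (about 76% power for 26%) on RV144 data alone.
- Add a sentence that the 26% figure relies on RV152 supplying 6-month counts for a substantial share of Visit 19 cases, and that losses among diagnosed volunteers would reduce power further.

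The cost is a text and table correction. No visit, sample size or analysis method changes, and the stated figure becomes slightly less favourable.

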#### 6.9.4.3 Correlates of protection and supplemental analyses.

**Cytotoxic T lymphocytes (CTLs).** Meaningful differences in CTL between infected and uninfected vaccine recipients would be difficult to detect. Only very large differences between the two groups would be detectable. To see this, if 20% of uninfected vaccine recipients develop CTLs (at a single time point) and a subset of 1000 uninfected recipients were assayed for CTL, then a study with 43 infected vaccine recipients would have 80% power to detect a significant difference if CTL rates were just 4.0% or less among infected vaccine recipients, using a two-sided two-sample comparison of proportions at significance level of 0.05. (Even if 5000 uninfected vaccine recipients were assayed for CTL, the study would have 80% power to detect a difference if CTL rates were just 4.3% or less among infected vaccine recipients.) Because of CTL test operating characteristics (sensitivity/specificity), CTL rates of approximately 5% or more are anticipated in both vaccine groups. Because of this and the relatively small expected number of infections among vaccinees, detecting CTL as a correlate of protection is not practical within current study parameters.

**Neutralizing antibody (Nab).** It may be possible to detect meaningful differences in Nab to T cell line-adapted or primary isolates, between infected and uninfected vaccine recipients. Development of neutralizing antibody will be compared between infected and uninfected vaccine recipients using a two-sided two-sample comparison of proportions. Assume for practical and economic reasons that only 150 of the uninfected vaccine recipients were assayed for Nab. Also assume that there are 43 infected vaccine recipients, as expected in the intent-to-treat analysis. Then if 70% of uninfected vaccine recipients develop Nab at a single time point, the study would have at least 93% power to detect a difference if Nab rates were 40% or less among infected vaccine recipients. If there are 33 infected vaccine recipients as expected in the per-protocol analysis, power would be 87% to detect the same difference.

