### **Phase III AIDSVAX® B/E and B/B Studies**

Phase III trials of AIDSVAX® B/B in North America and Europe (25) and AIDSVAX® B/E in Bangkok (26), are assessing the efficacy of these vaccines in high-risk populations in North America/Netherlands (mostly homosexual men) and Bangkok, Thailand (intravenous drug users). The North American/European trial was completed in late 2002 with results showing negligible efficacy overall (ITT efficacy = 5.7%, CI: -17% to 24%) with evidence suggestive of higher efficacy among women and some racial groups. The efficacy of AIDSVAX® BE gp120 vaccine in another trial among injecting drug users in Bangkok, Thailand in late 2003 showed no efficacy

when it was used by itself, i.e. when it was not used in combination with another vaccine. As of February 2003, nearly 5000 trial participants have received either AIDSVAX® B/B or AIDSVAX® B/E candidate vaccines with more than 33,000 doses of the vaccines administered. An independent DSMB has reviewed VaxGen's phase III trials every six months. Each trial has had seven DSMB safety reviews and received a positive safety review on each occasion. There have been two vaccine-related SAEs in the B/B trial, both being cases of cellulitis at the injection site that resolved with treatment, and no vaccine-related SAEs in the B/E trial. Two cases of Guillian Barre syndrome have been reported among recipients of AIDSVAX®, one with B/B in the North American phase III trial and one in the RV135 phase II trial using ALVAC-HIV prime and AIDSVAX® B/E boost. Neither were considered related to vaccine. Social harm monitoring in both phase III trials show acceptable levels (27,28).

It is noteworthy that the study design of the trial being proposed here would differ from the current phase III trial being conducted in Thailand among high-risk intravenous drug users in that volunteers would be from communities with a low-incidence of HIV infection, and most HIV transmissions would be expected to be via heterosexual routes.

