#### 6.9.7. Additional Laboratory Studies and Data Analysis

RV144 assessed volunteer risk behavior at baseline and follow-up using a self-administered behavioral questionnaire. Based on this assessment, 89% of volunteers reported one or less sexual partners and less than 5% reported high risk behavior (96). Hepatitis B can be transmitted through percutaneous or sexual exposure. Hepatitis C transmission almost exclusively occurs after percutaneous exposure. These two infections are common in MSM and intravenous drug users. In addition, hepatitis C in intravenous drug users is associated with HIV infection. In Thailand, men who become HIV infected have a significantly higher rate of HCV infection (97). Herpes Simplex Virus – 2 (HSV-2) is also transmitted sexually and its prevalence is associated with past sexual activity. In addition, HSV-2 infection is associated with a two to fourfold increase risk of HIV acquisition (98). To better characterize a volunteer's behavioral risk classification during the trial and its impact on HIV acquisition and vaccine efficacy, we plan to analyze biomarkers (serology to HBV, Hepatitis C, HSV-2, syphilis) associated with HIV acquisition and high risk behavior using stored volunteer samples unlinked to any personal identifiers.

To evaluate whether pre-existing immunity against vaccine vector impacts on vaccine immune responses, we are also proposing to conduct anti-ALVAC antibody assay using stored volunteer samples.

The STEP study which tested a replicating defective Ad5 vector expressing HIV-1 Gag, Pol, and Nef found volunteers who received the vaccine and had high levels of pre-existing Ad5 antibody were at greater risk for acquiring HIV as compared to volunteers who received placebo (99). One possible mechanism for this enhancement in HIV infection is the preferential expansion by Adenovirus of memory CD4 T cell with mucosal homing phenotype that increases susceptibility to HIV infection in individuals with prior Adenovirus immunity (100). It is unclear whether this mechanism is specific to Adenovirus vector only or may apply to other non-replicating viral vectors. Analysis of RV144 result specifically did not show enhancement in HIV infection. However to exclude the possibility of uneven distribution of this potential confounder, we will conduct Ad5 antibody assay using archived samples.

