Both Ad5 and anti-ALVAC antibodies will be determined using well established luciferas-based virus neutralization assay (101,102). Each assay will require 200ul of plasma. To determine distribution of baseline pre-existing Ad5 and anti-ALVAC antibodies, 200 random samples (100 placebos and 100 vaccinees) will be tested at baseline and 4 weeks post final vaccination.

As part of the pre-specified primary immunogenicity analysis, we have already conducted post vaccination CD4+ HIV-Specific intracellular cytokine staining (ICS), gp120 and p24 binding antibody; and lymphoproliferative assays on approximately 150 vaccine and 50 placebo recipients (96). Anti-ALVAC antibody assays will be conducted on the 150 individuals who received vaccine. To assess the impact of pre-existing anti-vector antibody on immunologic response, we intend to compare the proportion with ICS response and geometric mean binding antibody by presence or absence of pre-existing anti-ALVAC antibody.

To assess the impact of pre-existing on HIV acquisition, we intend to conduct a case control study comparing prevalence of baseline Ad5 and anti-ALVAC antibodies between volunteers who acquired HIV infection (case) and volunteers who remained free from HIV infection (controls). Controls will be matched to cases by gender, age and risk behavior at a 2:1 ratio.

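### The neutralizing-antibody correlate analysis in section 6.9.4.3 is a crude infected-versus-uninfected test; adjusting it for gender, age and baseline risk is a low-severity, cheap improvement

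*Protocol*

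**What the plan says.** Protocol section 6.9.4.3, under neutralizing antibody (Nab), names the method: "Development of neutralizing antibody will be compared between infected and uninfected vaccine recipients using a two-sided two-sample comparison of proportions". It gives no covariate, stratum or matching factor. For the group sizes it says "Assume for practical and economic reasons that only 150 of the uninfected vaccine recipients were assayed for Nab" and "Also assume that there are 43 infected vaccine recipients, as expected in the intent-to-treat analysis". It takes a 70% response in the uninfected against 40% or less in the infected and states power of at least 93%. For the smaller set it says: "If there are 33 infected vaccine recipients as expected in the per-protocol analysis, power would be 87% to detect the same difference". The test level is stated for the CTL calculation in the same section, "using a two-sided two-sample comparison of proportions at significance level of 0.05", and I assume that it also applies to Nab.

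Section 6.9.7 plans a case-control study of baseline Ad5 and anti-ALVAC antibody against HIV acquisition. There, "Controls will be matched to cases by gender, age and risk behavior at a 2:1 ratio". Nothing elsewhere in the protocol adds adjustment or matching to the Nab comparison.

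**The concern.** The comparison is observational. Infected and uninfected vaccinees are defined by something that happens after randomization. Section 6.9.3.2 recognises the same difficulty for viral load: it warns that randomization does not support significance levels in groups selected this way, and it plans protection against selection bias. Section 6.9.4.3 has no such safeguard, although gender, age and a Visit 1 risk questionnaire are available for every volunteer.

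If one of these factors predicts both infection and Nab response, the crude test can produce a spurious correlate or hide a real one, and the nominal 5% level no longer holds. The result has some weight. Section 9.2 first makes correlate work conditional on efficacy, then reports modest efficacy and treats finding correlates as essential, with neutralizing antibody among the humoral assays.

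**Working it through.** **Inputs from the protocol.** 43 infected vaccinees (intent-to-treat) or 33 (per-protocol), 150 uninfected, response 70% against 40% (6.9.4.3). On risk behavior, "less than 5% reported high risk behavior" (6.9.7). HSV-2 carries a two- to fourfold HIV risk (6.9.7).

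**Assumptions.** Two-sided 5% level. 5% taken as the upper limit for high-risk behavior. The fourfold HSV-2 figure used as a stand-in for the effect of reported risk behavior. The gap in Nab response between levels of a factor, which the protocol does not give.

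**Step 1: reproduce the stated power.** Continuity-corrected normal approximation: power = Φ[(d − c − 1.96·SE₀)/SE₁], with d = 0.30, c = ½(1/n + 1/150), SE₀ pooled and SE₁ unpooled.
- n = 43: SE₀ = 0.0834, SE₁ = 0.0836, c = 0.0150. Power = Φ(1.456) = 92.7%, against a stated figure of at least 93%.
- n = 33: SE₀ = 0.0920, SE₁ = 0.0931, c = 0.0185. Power = Φ(1.088) = 86.2%, against a stated 87%.

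The stated figures are sound for the crude test.

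**Step 2: false rejection when Nab has no effect within levels of the factor.** For a binary factor with prevalence f and infection risk ratio RR, its share among the infected is f·RR/(f·RR + 1 − f). The spurious difference is (share among infected − f) × Nab gap. Rejection = Φ[(d − 1.96·SE₀)/SE₁] + Φ[(−d − 1.96·SE₀)/SE₁], without continuity correction, holding the uninfected response at 70%.

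For reported risk behavior, the share among the infected is 0.05×4/(0.05×4 + 0.95) = 0.20/1.15 = 17.4%, an excess of 12.4 points.

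| Factor | RR | Assumed Nab gap | Spurious difference | Rejection, 43 vs 150 | Rejection, 33 vs 150 |
|---|---|---|---|---|---|
| f = 5% | 4 | 0 | 0 | 5.0% | 5.0% |
| f = 5% | 4 | 10 points | 1.2 points | 5.4% | 5.4% |
| f = 5% | 4 | 30 points | 3.7 points | 7.9% | 7.5% |
| f = 50% (such as gender) | 2 | 10 points | 1.7 points | 5.7% | 5.6% |
| f = 50% | 2 | 30 points | 5.0 points | 10.1% | 9.3% |
| f = 50% | 4 | 30 points | 9.0 points | 20.8% | 18.1% |

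The 50% rows rest entirely on assumed values.

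**Step 3: cost of adjustment.** Multiply the variances in step 1 by 1/(1 − R²), where R² between Nab and the covariates is assumed.
- R² = 0.05: 91.5% (43 infected) and 84.4% (33 infected).
- R² = 0.10: 90.0% and 82.4%.

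**Step 4: a separate problem, for scale.** Sections 6.9.3.2 and 6.9.4.2 expect 10 of the 43 infected vaccinees to be infected before complete immunization. If their Nab rate is assumed to be 0% to 50%, with 70% in the other 33, the infected rate is (33×0.70 + 10×0)/43 = 54% up to (33×0.70 + 10×0.50)/43 = 65%. The crude test then rejects 51% down to 9.5% of the time with no protective effect.

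**The case against.** The strongest reply is that the second link is missing. A reader might infer that because infected and uninfected vaccinees differ in risk, the crude test must yield a false correlate. That does not follow: with a fourfold risk factor and no Nab gap, the error stays at 5.0%. The protocol gives no Nab response by gender or age. Its one relevant report, the phase II vCP205 trial in section 4, found no significant difference in immune responses between higher- and lower-risk groups. That trial used another construct, did not address gender or age, and does not prove absence of a difference, but it points weakly against a link with risk. This part of the objection stands and limits the point to low severity.

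A reader might also cite the earlier AIDSVAX B/B trial, with its "evidence suggestive of higher efficacy among women and some racial groups", as evidence that gender matters here. That statement is about efficacy and says nothing about antibody response, so it does not supply the link.

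The parallel with section 6.9.7 has limits. That study concerns antibody present before vaccination and uses 2:1 matching. It is not a frequency-matched draw of the uninfected sample. It shows that the protocol regards these factors as relevant to an antibody-versus-acquisition question, and no more.

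Finally, the analysis is supplemental, no success claim rests on it, the 150 is a power assumption, and covariates and sampling are often left to an analysis plan, which is not at hand. This too lowers the severity. It does not remove the point, because the protocol names the crude test as the method.

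**Conclusion.** The concern holds at low severity. The protocol fixes a crude comparison of groups formed after randomization, where a better analysis is available from data already collected. Under the stated assumptions the inflation attributable to reported risk behavior is small, about 5% to 8% false rejection against a nominal 5%. Larger values, 10% to 21% with 43 infected, need a common factor such as gender combined with an assumed 30-point Nab gap, which nothing in the protocol supports. If Nab does not vary with the factor, there is no inflation. The largest spurious difference in these scenarios, 9 points, is well below the 30 points in the power statement. The stated power figures are not in error.

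**What to change.** In section 6.9.4.3, make the main Nab comparison a logistic regression of infection status on Nab among vaccine recipients, adjusted for gender, age and baseline risk behavior. Keep the two-sample comparison of proportions as descriptive. Optionally, draw the uninfected sample within strata of the same factors and keep the strata in the model.

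The cost is one or two sentences of text and, if chosen, a stratified draw of archived specimens, with no new visits or assays. With 150 uninfected vaccinees retained, the loss of precision is the modest one shown in step 3 of the working.

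This change does not deal with the vaccinees infected before complete immunization (step 4). That needs its own handling in the intent-to-treat version.
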